**Session 1**
Introduction (5-8 minutes)Alcohol and health factsheet (10 minutes)Review current alcohol use (15 minutes)Complete change plan (10 minutes)Diaphragmatic breathing (8 minutes)Wrap up and schedule next session (5 minutes)
**Session 2**
Recap of past session, check-in, and agenda setting (5 minutes)Review weekly drinking data and change goals from last week (10 minutes)Review strategies for managing triggers (20 minutes)Urge surfing skill (10 minutes)Wrap up and schedule next session (5 minutes)
**Session 3**
Recap of past session, check-in, and agenda setting (5 minutes)Review weekly drinking data and change goals from last week (10 minutes)Strategies for reducing alcohol-related harm (20 minutes)Before known drinking occasionsWhile drinking alcoholAfter drinking alcoholWrap up and schedule next session (5 minutes)
**Session 4**
Recap of past session, check-in, and agenda setting (5 minutes)Review weekly drinking data and change goals from last week (5-8 minutes)Review overall progress (5-8 minutes)Set goals and plan for going forward (10-15 minutes)Wrap up and give reminder of remaining study tasks (5 minutes)

##### TRAC-ER Participants

###### Overview

Participants will complete all aspects of the TRAC intervention condition. In addition to receiving triggered surveys when they leave a risky location, participants will also receive prevention messaging when they first arrive at a risky location. This messaging will be tailored based on the data collected regarding participants’ risky locations and the strategies to address triggers discussed during the MI intervention sessions. In addition, if participants return a breathalyzer reading >0.00%, they will receive harm reduction messaging encouraging them to engage in protective behaviors. These messages will continue throughout the 2-month intervention period, including after the 4 TRAC sessions have been completed. Participants will complete the T1 to T4 assessments following the schedule described for SAM-only participants.

###### MI Interventionist Training and Fidelity Assessment

The full-time study interventionist, an individual with a master’s degree in counseling, will receive refresher training from a supervisor who is a licensed clinical social worker regarding the principles of MI as they relate to substance use and the key components of the TRAC intervention through 12 hours of instruction and mock interviews. This supervisor will review the interventionist’s first TRAC case (or additional cases, if needed). Fidelity ratings will be conducted using a combination of the Motivational Interviewing Treatment Integrity (MITI) 4.2.1 coding system and adherence checklists to be developed by the study team to code for the presence of specific skills and exercises included in the TRAC protocol. MITI is an established structured behavioral coding system that serves as a treatment fidelity measure for clinical trials of MI [37,38]. It provides a global impression of empathy and MI spirit, a reflection-to-question ratio, and summary scores for MI components based on behavior count ratios of complex reflections, open questions, and MI-adherent utterances. The interventionist will be *certified* as able to deliver the protocol with fidelity. Certification will involve meeting adherence of at least 80% of TRAC-specific skills and exercises and the recommended MI competency threshold on at least 80% of sessions for a given case. Until the interventionist is certified, the supervisor will review entire session recordings weekly to code TRAC adherence, and a randomly selected 20-minute segment will be coded with MITI. Individual feedback and training will be provided weekly. Overall trial fidelity ratings (adherence to TRAC skills and exercises and MI competency) will be determined via review of an additional randomly selected 20% of interviews (10% from each site), in line with recommendations for RCTs of MI [39], including double coding by the supervisor and a research assistant, both of whom will be certified in MITI coding.

##### Data Collection Procedures

###### Overview

As this study is examining both short- and long-term effects and comparing them among the groups, the primary end point of the number of past-month drinking days will be assessed based on SAM results collected before T1, throughout the intervention, and before T3 and T4. Secondary end points include drinks per drinking day and binge drinking episodes. All other variables measured, including those related to HIV risk behaviors, will be used to conduct exploratory analyses. The sources of data for this RCT include SAM data (including surveys and breathalyzer results, discussed in detail previously), baseline and follow-up self-report measures (T1-T4), HIV and STI testing, app-based process measures, and qualitative interviews.

###### Baseline and Follow-Up Measures

An assessment battery will be administered to all participants at T1, T2, T3, and T4. This will include several measures of alcohol use as well as more exploratory variables, including alcohol cravings, alcohol consequences, the use of alcohol treatment services, HIV risk behaviors, and experiences of discrimination related to participants’ identity as sexual and gender minority individuals. Table 2 presents a description of the key study measures.

**Table 2 table2:** Description of key study measures.

Construct and time		Measure	End point	Description
Drinking days, 2× daily		Breath alcohol content	Primary	BACtrack Mobile breathalyzer result sent via mobile app; measured 2× daily for 8 weeks during the intervention and for 1 month before T1^a^, T3^b^, and T4^c^; 2 negative readings per day=nondrinking day
Drinks per drinking day, daily		Self-reported alcohol use through app	Secondary	3 items: alcohol consumed (yes or no), number of drinks, and time spent drinking; measured daily during the intervention and for 1 month before T1, T3, and T4
Binge drinking episodes, daily		Self-reported alcohol use through app	Secondary	Occasions when participants had ≥5 drinks based on self-reported number of drinks; measured daily during the intervention and for 1 month before T1, T3, and T4
Alcohol withdrawal symptoms, daily		Single-item AWSC^d^ [40]	Exploratory	1 item: alcohol withdrawal symptom severity on a scale of 0 to 9; those scoring ≥2 are asked to complete the 17-item AWSC, which assesses the severity of symptoms; measured daily during intervention and for 1 month before T1, T3, and T4
Sexual activity, daily		Self-reported through app	Exploratory	6 items: past-day sexual activity, number of partners, partner type, partner HIV status, type of sexual activity, condomless sex, and PrEP^e^ use
Location characteristics, up to 2× daily		Self-reported through app	Exploratory	12 items assessing alcohol and substance use, sexual behaviors, peer use of alcohol or substances, and harassment or discrimination experienced
Alcohol use, T1, T2^f^, T3, and T4		PROMIS^g^ Short Form–Alcohol Use 7a [41]	Exploratory	7 items that assess general alcohol use and problem drinking in the past 30 days (eg, drank too much and drank heavily)

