Every morning during the SAM periods, participants will receive a push notification asking them to report the number of drinks consumed in the previous day (if applicable), time spent drinking, alcohol withdrawal symptoms, and sexual risk behaviors. The app will also send requests for breathalyzer readings at least 2 times per day in response to visits to risky locations and through random requests. At the time of providing the breathalyzer reading, participants will also complete a brief mobile survey using the study app that includes questions related to their alcohol use. Participants can view a log of their breathalyzer readings in the app. Participants will have the option to report a trigger in the app and provide details about the trigger, including the location where the trigger was generated. Participants who are randomized to the TRAC-ER intervention will receive a harm reduction message based on the type of trigger (social, emotional, or other) they report. A guided breathing exercise and urge surfing exercise are included in the app for those in the TRAC and TRAC-ER conditions. Figure 1 presents a screenshot of the app. If, at any point during the monitoring periods, the app stops collecting GPS data, the study team will reach out to determine whether the participant accidentally turned off location tracking, lost their mobile phone, or is experiencing other technical difficulties.

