**1-30**				
	Morning survey: sent between 7 AM and 10 AM (based on participant preference)	✓	✓	✓
	Random breathalyzer reading and breathalyzer request survey: request at a random time between 11 AM and 5 PM and at a random time between 5 PM and 11 PM	✓	✓	✓
	Location survey and breathalyzer reading: request breathalyzer survey and breathalyzer reading when participant leaves a risky location	✓	✓	✓

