**31-90**				
	Morning survey: sent between 7 AM and 10 AM (based on participant preference)	✓	✓	✓
	Random breathalyzer reading and breathalyzer request survey: request at a random time between 11 AM and 5 PM and at a random time between 5 PM and 11 PM	✓	✓	✓
	Location survey and breathalyzer reading: request breathalyzer request survey and breathalyzer reading when participant leaves a risky location	✓	✓	✓

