##### Data Analysis Plan

###### Analysis of Alcohol Use Outcomes

Descriptive statistics for breathalyzer reading data will be summarized overall, by group (SAM only, SAM+TRAC, and SAM+TRAC-ER) and across time periods (T1-T4). The primary outcome is the number of drinking days in the past month, which is defined as the days on which individuals did not report 2 negative breathalyzer results. The rate of drinking (incidence of drinking) is the number of drinking days observed within the past month. The secondary outcomes include the number of drinks per drinking day, the number of days with binge drinking episodes, and the number of days for which HIV risk behaviors occur. All these outcomes are count data. The goal of this analysis is 2-fold: first, short-term analysis at the end of the 2-month intervention period, and, second, long-term analysis at the end of 9 months. We will fit a generalized linear model [50], with a general formulation for count data as follows:

g(E(y_i_)) = g(μ_i_) = x'_i_β (1)

where *y_i_* is the outcome variable for (*i*=1,2,3,...,*n*), *n* is the total number of observations, *μ*_i_=*E*(*y_i_*) is the expected count, *g* is the link function (a mathematical function connecting the counts with the explanatory variables), *β* is a vector of regression parameters to be estimated, and *x_i_* is a vector of independent covariates to be included in the model. These covariates include group, time, age (or age group), gender identity, sexual orientation, and site.

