Our study has promising strengths, but it must be considered in light of several limitations. While the use of ecological momentary assessment (EMA) provides advantageous opportunities for real-time trigger location data and convenience reporting through smartphones, prior EMA studies highlight the potential exhaustion that participants may experience, which may reduce the level of participation. This study may further explore convenient assessment windows to diminish the intensity of EMA sampling. In addition, as previously mentioned, SMMT communities experience unique sociostructural challenges, such as unemployment, homelessness, forced displacement, and community violence [59]. These systems of power may operate dynamically and render difficulties in participating fully and equitably in hazardous alcohol use prevention programs [60]. Finally, the real-time tracking of alcohol use behaviors of participants may give rise to reporting bias. In the context of alcohol-related stigma, social desirability biases may subject participants to aligning their responses to the expectations of societal norms around alcohol consumption; however, the use of breathalyzers will help to protect against self-report bias.

Prior studies have also reported concerns for temporal bias, where participants were reluctant to complete location- and time-based–triggered EMA surveys due to the inconvenient times at which the surveys were sent. Similarly, EMA studies related to substance use have mentioned challenges with the time frame for EMA sampling [61]. In this study, EMA assessments will occur between 11 AM and 11 PM to avoid disturbing participants. However, participants in prior studies have discussed that these hours may not be representative of the time frames when drinking occurs because alcohol use may occur later at night, along with variations in mood and social activities. Thus, we may explore the potential options for personalized hours of EMA sampling for participants. Breathalyzer device loss may also pose a challenge. However, unlike prior EMA studies that distributed mobile phones and experienced challenges with device loss [62], our study enables participants to use their existing smartphones to use the app, which will reduce instances of device loss or misplacement.

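### The two-negative-readings rule for the primary endpoint misses drinking that starts after the evening reading and, read literally, ignores a positive location-exit reading; the role of the morning report needs reconciling

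*Protocol article*

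**What the plan says.** The rule appears twice in the protocol article. In Baseline and Follow-Up Measures, Table 2, the entry for drinking days reads "2 negative readings per day=nondrinking day". In Analysis of Alcohol Use Outcomes, the primary outcome is "defined as the days on which individuals did not report 2 negative breathalyzer results". Neither statement mentions a positive reading or a self-report.

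Table 1 gives the timing of the scheduled pair in every monitoring block: "request at a random time between 11 AM and 5 PM and at a random time between 5 PM and 11 PM". All three arms also have an exit prompt: "request breathalyzer survey and breathalyzer reading when participant leaves a risky location". Description of TRAC-ER Study App says the app sends "requests for breathalyzer readings at least 2 times per day in response to visits to risky locations and through random requests", so a day may hold more than two readings.

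The same section describes a morning notification "asking them to report the number of drinks consumed in the previous day". Table 2 lists these self-report items against the secondary endpoints (drinks per drinking day, binge episodes) and not against drinking days. Yet the Abstract (Methods) and Study Design name breathalyzer results and daily self-reports together as the basis for the primary and secondary outcomes. The overview of Data Collection Procedures bases the primary endpoint on SAM results and describes SAM data as surveys plus breathalyzer results.

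In the Discussion (Summary), the 11 AM-11 PM window is listed as a limitation. Citing participants in prior studies, it says that "these hours may not be representative of the time frames when drinking occurs because alcohol use may occur later at night". The only response offered is that personalized hours may be explored.

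**The concern.** A negative reading shows only that no alcohol was detected at that moment. Two negatives, the later one taken at any time from 5 PM to 11 PM, say nothing about the rest of the night. The rule nevertheless treats them as proof of a non-drinking day.

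The wording also gives a positive reading no priority. Two negative random readings and one positive exit reading still amount to two negatives. Elsewhere the protocol treats such a positive as alcohol use: in TRAC-ER, a reading above 0.00% triggers a harm reduction message. A participant could receive that message on a day the primary endpoint records as non-drinking.

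The next-morning drink report covers the same day and is collected in every arm. As defined, one day can be non-drinking for the primary endpoint and a binge day (at least 5 drinks) for a secondary one. At stake are the sensitivity of the primary endpoint, its consistency with the secondary endpoints, and whether it matches what the Abstract and Study Design say it measures.

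**Working it through.** **The plan's own figures.** The plan gives no figure for how well the rule detects drinking. Its recruitment target reproduces: 324 / (1 - 0.20) = 405. The power statement (at least 90%) also reproduces. A repeated-measures group-by-time test with effect size 0.071, N = 324, 4 visits and correlation 0.69 has noncentrality 0.071² × 324 × 4 / (1 - 0.69) ≈ 21.1 on 6 and 963 degrees of freedom, which gives 95.1%. This point changes neither figure.

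**Missed share under the current rule.** From Table 1, the evening request is at a random time between hours 17 and 23. The assumptions are mine: the request is uniform on that interval, the response is prompt, there is one drinking episode starting at hour s (17 or later), alcohol stays detectable through 11 PM, and there is no exit reading. Both scheduled readings are then negative when the evening request comes before s:

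missed share = (s - 17) / 6

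| Start | s | Missed share |
|---|---|---|
| 7 PM | 19 | 2/6 = 33% |
| 8 PM | 20 | 3/6 = 50% |
| 9 PM | 21 | 4/6 = 67% |
| 10 PM | 22 | 5/6 = 83% |
| 11 PM or later | 23 or more | 100% |

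**Relaxing the prompt response.** Ethical Considerations pays for samples submitted within 90 minutes. If every reading came the full 1.5 hours late, the share would be (s - 18.5) / 6: 25% at 8 PM, 42% at 9 PM, 58% at 10 PM and 75% at 11 PM. The loss is smaller but still substantial.

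**Effect on the comparison.** Short-Term Outcome Analyses specifies a log link with a Poisson or negative binomial distribution, so the estimated contrast is a rate ratio. Assume true means of 12 and 9 days and no false positives.
- Equal sensitivity of 50%: 12 × 0.5 = 6 and 9 × 0.5 = 4.5. The difference falls from 3 to 1.5 days; the ratio stays at 9/12 = 4.5/6 = 0.75.
- Unequal sensitivity: observed ratio = true ratio × (sensitivity in the intervention arm / sensitivity in control). With 50% against 70%, 4.5/8.4 = 0.54. With 70% against 50%, 6.3/6 = 1.05. The bias can run in either direction.

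**With the morning report added.** If the report detects a share q of drinking days, independently of the readings, the missed share becomes (s - 17)/6 × (1 - q). The documents do not give q. Over an assumed range of 0.70 to 0.95, a 9 PM start falls from 67% to between 20% and 3.3%, and an 11 PM start from 100% to between 30% and 5%. The error is reduced, not removed.

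**The case against.** **Self-report may already be intended.** The Abstract, Study Design and Data Collection Procedures link surveys to the primary outcome, so a reader should not conclude that the protocol has settled on using the morning report for secondary outcomes only. This stands. It makes the problem an inconsistency, because no combination rule is stated and both operative definitions use breath alone.

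**The positive-exit case may be an artefact of shorthand.** Table 2 describes a twice-daily measure, and its entry may simply mean that all of the day's readings are negative. A reader might infer that the trial means to discard positive exit readings. No text says so; it is a gap in the wording.

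**Bias in favour of the intervention is not shown.** It is tempting to argue that the intervention targets evening drinking and so changes detection by arm. The protocol ties its messages to risky locations and reported triggers, not to a time of day. Differential detection remains only a possibility.

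**Halving a 3-day difference is not bias in the model's estimate.** This also stands: under equal sensitivity the rate ratio is unchanged. The start times, the 50% sensitivity and the 3 days are all assumptions. The table leaves out exit readings, and it leaves out evening drinkers who skip a reading, whom the analysis-section wording would count as drinking.

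**Breath-only measurement is a defensible choice.** Participants in two arms review their drinking data with an interventionist each week, and the Discussion names social desirability bias with the breathalyzer as protection. Under-reporting in the counselled arms could make a composite exaggerate benefit. This is a real trade-off and the reason to keep the breath-only analysis. It is no reason to let two negatives outweigh a positive reading.

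**The time window is disclosed.** It is, but disclosure leaves the rule unchanged.

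**Conclusion.** The concern holds in a limited form. As written, the primary endpoint scores a day as non-drinking when drinking starts after the evening reading and, on the literal wording, even when an exit reading is positive. The statements that self-reports contribute to the primary outcome conflict with the two operative definitions and must be reconciled with them.

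The illustrated loss is 33% of drinking days with a 7 PM start, 67% with a 9 PM start and 100% from 11 PM, under the assumptions in the working. It is not an estimate for this trial, because the documents give no distribution of drinking times. With equal detection across arms and no false positives, the cost is smaller absolute differences and lower precision, with the rate ratio intact. A distorted ratio requires detection to differ by arm, which nothing in the documents establishes.

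**What to change.** 1. State in Table 2 and in Analysis of Alcohol Use Outcomes that any positive breath reading, random or location-exit, makes the day a drinking day whatever the other readings show. Add a sensitivity analysis on random readings only, because the number of exit readings depends on the places visited.
2. Prespecify the composite: any positive reading, or at least 1 drink in the next-morning report. Make it either the primary definition, in line with the Abstract and Study Design, or a key sensitivity analysis. Report it beside the breath-only result in both cases, and say how a day with a missing morning survey is handled.
3. Align the Abstract, Study Design, Data Collection Procedures, Table 2 and the analysis section on which data define a drinking day.

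The cost is wording and one or two additional analyses. All the data are already collected daily in every arm during monitoring, and the sample size does not change. The downside is that the composite brings in self-report, which may be under-reported differently in the counselled arms, so the breath-only analysis must be kept. The change should be made before outcome data are examined.

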###### Scientific Rigor

The proposed study uses a rigorous randomized comparative effectiveness trial design to assess intervention effects on alcohol use outcomes. The following characteristics add to the rigor of the study: (1) the use of a SAM-only control group so that all groups can be compared using daily-level alcohol use data, (2) the incorporation of breathalyzers to enhance the validity of self-reported alcohol use, (3) the inclusion of follow-up self-report and SAM data to assess long-term outcomes, (4) recruitment strategies that use in-person and web-based methods to enhance the diversity of the sample, (5) the inclusion of a dedicated biostatistician to provide rigorous outcome analyses, (6) support from app programmers to customize the app and address technical issues, and (7) the inclusion of a licensed social worker to ensure high-quality MI training and fidelity.

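### Drinks per drinking day and binge episodes rest on self-report that could differ by arm, and the claimed breathalyzer safeguard directly covers only drinking days

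*Protocol article*

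**What the plan says.** **Endpoints.** Table 2 (Baseline and Follow-Up Measures) gives breath alcohol content as the measure of drinking days, with the rule "2 negative readings per day=nondrinking day". Both secondary drinking endpoints have app self-report as their measure. Drinks per drinking day uses "3 items: alcohol consumed (yes or no), number of drinks, and time spent drinking". Binge episodes are "Occasions when participants had ≥5 drinks based on self-reported number of drinks". The section on the study app says that the count is collected by a morning notification "asking them to report the number of drinks consumed in the previous day".

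**Sessions.** The overview of the TRAC sessions lists, for Session 2, "Review weekly drinking data and change goals from last week". Sessions 3 and 4 have the same item, and Session 4 adds a review of overall progress. Table 1 ticks the sessions for TRAC and TRAC-ER and leaves the control column blank.

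**Safeguard.** Scientific Rigor lists "the incorporation of breathalyzers to enhance the validity of self-reported alcohol use" among the strengths. The Discussion admits reporting bias and social desirability bias and answers: "however, the use of breathalyzers will help to protect against self-report bias". Neither statement is limited to drinking days, and neither section treats the bias as something that might differ between arms.

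**The concern.** Two features of the design meet in the secondary drinking endpoints.

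First, the safeguard against self-report bias is stated in general terms, but the measurement table gives the breathalyzer a role only in the drinking-day outcome. The article describes no check of reported drinks against readings.

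Second, the arms report under different conditions. TRAC and TRAC-ER participants discuss their drinking data and their goals with a counselor; SAM-only participants do not. The article has no statement on blinding, but counseling sessions and in-app messages are evident to those who receive them. If reporting shifts with this contact, a difference in reported drinks or binges between an intervention arm and SAM-only would mix changed drinking with changed reporting, and the analysis as described could not separate the two.

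**Working it through.** **Step 1. What each outcome rests on.**

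| Outcome (Table 2) | Source | Can a reading verify it? |
|---|---|---|
| Drinking days (primary) | Breath readings | Yes, as drinking or not |
| Drinks per drinking day (secondary) | Self-reported count | No |
| Binge episodes (secondary) | Self-reported count, 5 or more | No |

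The breath rule yields a yes or no for the day. It carries no number of drinks.

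**Step 2. Trace one discordant day.** One of the day's two readings is above 0.00%, and the next morning's survey reports no alcohol for that day.
- Primary outcome: the day lacks two negative readings, so it is a drinking day under the definition in Analysis of Alcohol Use Outcomes.
- Binge episodes: the reported count is zero, so no binge is added.
- Drinks per drinking day: no drinks are added. The article does not say whether the denominator is breath-based or self-reported. If breath-based, the day enters as zero drinks; if self-reported, it drops out.

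The article states no rule for such a day; this is what follows if the reported count is used as it stands. A day with two negative random readings and a positive one on leaving a risky location is not addressed explicitly.

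**Step 3. Size of the loss.** Let *d* be the share of true drinking days that are denied in the survey.
- Breath-based denominator, denied days like the others: mean drinks per drinking day is multiplied by (1 − *d*).
- Self-reported denominator: the mean is unchanged if denied days are like the others, and falls if they are heavier.
- Binge count: multiplied by (1 − share of binge days denied).

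**Step 4. Between arms, with no true effect.** Apparent rate ratio = reporting completeness in the intervention arm ÷ completeness in SAM-only. For assumed completeness of 0.90 and 0.80 against 1.00 this gives 0.90 and 0.80. These ratios restate their assumption; they are a scale, not an estimate. Completeness that is better in the intervention arm gives a ratio above 1.

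**Step 5. What such a shift could do to a test (assumed values).** The article's sample size gives 405 × 0.80 = 324 analyzed, and 324 ÷ 3 = 108 per arm; the point disputes none of these. With a two-sided normal test at 5%, SE = SD × √(2/108), and the chance of significance is Φ(δ/SE − 1.96) + Φ(−δ/SE − 1.96).
- Drinks per drinking day, assumed control mean 5 and SD 2 to 3. A 10% shift is δ = 0.5; SE = 0.272 to 0.408; chance 45% to 23%. A 20% shift is δ = 1.0; chance 96% to 69%.
- Binge days, assumed control mean 4 per month and SD 3 to 4. A 10% shift is δ = 0.4; SE = 0.408 to 0.544; chance 17% to 11%. A 20% shift is δ = 0.8; chance 50% to 31%.

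The nominal rate is 5%. The means, SDs and shifts are not in the article. The calculation shows only that a modest difference in reporting need not be harmless at this sample size.

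**Step 6. When the review takes place.** Four weekly sessions from about day 31 end before day 60 if on schedule; with the 6-week allowance they end by about day 31 + 42 − 1 = 72. Monitoring runs to day 90. Table 2 measures both endpoints daily during the intervention, so the review overlaps part of that period. If the past-month window is applied at T2 (roughly days 61 to 90), most or all of it follows the last review.

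**The case against.** The case on the other side is substantial.

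- **The article is open about the measure.** Table 2 labels both endpoints as self-reported, and a breathalyzer cannot count drinks, so self-report is the natural source. The safeguard wording is hedged. Knowing that a reading is on record may deter flat denial, so indirect protection is not zero. All this stands. What remains is that the wording is not limited to the outcome that the readings directly protect.
- **Handling of discordant days belongs in an analysis plan, which is not shown.** This is fair, and silence on that rule is not the point. The point is the breadth of the stated safeguard set against the article's own measurement table; the added analysis can go in the analysis plan.
- **There is a second self-report.** A brief survey on alcohol use comes with each reading. It is still self-report and does not verify a count.
- **The check is partial.** A mismatch table finds denial, not under-counting such as six drinks reported as four. Random requests run from 11 AM to 11 PM, and the Discussion notes that drinking may occur later. This stands and limits what the fix can claim.

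A reader might infer that the bias favors TRAC and TRAC-ER. The article does not support that. It does not say whether the weekly drinking data reviewed in sessions are self-reports, breath readings or both. Review of breath readings could make denial harder in those arms, and counseling could improve the counting of drinks. A reader might also want short-term secondary results believed only if months 6 and 9 agree. The article deliberately separates short-term from long-term analysis, and such a condition would discount a real effect that fades.

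**Conclusion.** The point holds in a limited form. Both secondary drinking endpoints rest on self-report, the counselor's review of drinking data occurs only in TRAC and TRAC-ER, and the stated breathalyzer safeguard directly protects only the drinking-day outcome. A day with a positive reading and a denial can therefore count as drinking in the primary analysis while adding no drinks or binges to the secondary ones.

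Reporting could differ by arm, but neither its direction nor its size can be derived from the article, and the ratios and error rates above are illustrations under assumed values. The conclusion rests on two readings: that participants know their arm, which is inferred from the interventions, and that the reported count is used as it stands on discordant days. The primary endpoint is unaffected. The matter is worth correcting because the data needed are already collected, but it does not threaten the trial's main conclusion.

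**What to change.** 1. Tabulate by arm and period the share of days with a reading above 0.00% on which the survey covering that same day reports no alcohol. Use actual positive readings, not days classed as drinking because a reading is missing.
2. In a prespecified sensitivity analysis of drinks per drinking day and binge episodes, treat those days as drinking days with an unknown drink count, handled by the multiple imputation already planned, and not as zero-drink days. Leave the main analysis as it is.
3. In Scientific Rigor and in the Discussion, limit the breathalyzer safeguard to the breath-based outcome. State that the secondary drinking results remain open to differential reporting, since the check finds denial but not under-counting.

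The cost is a little more analysis of data already collected, slightly wider intervals in the sensitivity analysis, and a change of wording.
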